## 16.7 APPENDIX VII. DESCRIPTION OF OTHER CLINICAL AND LABORATORY METHODS

5. This section 'Appendix VII. Description of other clinical and laboratory methods' of the appendix, describes the clinical and laboratory based assays for some secondary endpoints conducted in subgroups of women in specific study sites or otherwise in a random sample of women in all sites. These volume and timing of these samples is described in 'Table 1: Summary Table of Study Design and Schedule of Assessment' and in sections 4, page 15, and in section 4 'PARTICIPANTS TIMELINE', page 33 onwards. The purpose of this appendix text is to describe the assays and measures of the procedures in more detail.

### 16.8.1 Impact on maternal and neonatal anthropometric and biochemical markers of nutritional status

**COLLABORATING INSTITUTIONS AND CONTACT PERSONS:** [name] (COM, University of Malawi); [name] (University of Tampere, Finland); [name] and [name] (University of Melbourne, Australia)

**OBJECTIVE:** To evaluate the impact of adding AZ to IPTp-DP on maternal and neonatal anthropometric and biochemical markers of nutritional status and maternal intestinal inflammation.

**RATIONALE:** Previous trials showed that AZ results in general effects on maternal health including gains in gestational weight, maternal body mass index (BMI) and mid-upper arm circumference (MUAC). If this is confirmed in the current trial, it will be important to examine whether this is through improved intestinal nutrient absorption, for example through reduction in gut inflammation or effects on gut microbe populations, or whether this simply reflects the reduced rate of infections which reduces maternal energy expenditure. Neonatal antibiotic use has been associated with the development of obesity in later life, possibly through effects on the neonatal intestinal microbiome. Less is known about the impact of gestational antibiotic use on maternal and neonatal nutritional status.

Improved maternal and neonatal nutritional status as a result of gestational antibiotic exposure could be beneficial, given maternal undernutrition and low birthweight remain enormous health problems, in particular in developing countries. Furthermore, nutritional depletion as a result of pregnancy (and e.g. pregnancy-associated infections) remains an issue in low-resource settings, and could potentially be averted through secondary effects of gestational antimalarial/antibiotic use. More epidemiological and mechanistic evidence for a role of gestational antibiotic use in shaping short- and long-term maternal and neonatal nutritional status is urgently required in order to rule out adverse effects such as later-life obesity (both mother and neonate) and to firmly establish benefits such as improvements in maternal nutritional status that will benefit the fetus and neonate. We will also measure aflatoxin levels as potential confounder because recent evidence from both animal and human studies has shown a significant association between aflatoxin and impaired growth.

**METHODS:** *Nutritional assessment methods (anthropometric, other):* Detailed assessments of maternal and neonatal body composition will be done in a subset of women. The following routine anthropometric measurements will be taken from the mother: weight, height, MUAC, skinfold thickness (SFT) with standard Harpenden calipers, hip and waist circumference, and from the newborn: weight, head circumference, abdominal circumference, length, SFT). SFT will be measured using (Holtain, UK). In addition, mothers' postpartum body composition, particularly % body fat, will

be evaluated using the non-invasive technique of segmental multifrequency bioelectrical impedance analysis (BIA) using Tanita body composition monitors (Tanita, Japan). Newborn/infant % body fat will be assessed using the non-invasive technique of Near Infrared Interactance device to determine body composition. Postpartum maternal and neonatal nutritional composition will further be evaluated using a stable isotope techniques have been used in studies of human nutrition for over 50 years. Deuterium is a stable (non-radioactive) isotope of hydrogen. It is given orally as deuterium oxide ( $2^{\text{H}}\text{H}_2\text{O}$  or 'labeled water'), and after mixing with body water, it is eliminated from the body in urine, saliva, sweat and human milk. Deuterium oxide is handled in the body in the same way as water, and is dispersed through the body water within a matter of hours. Through measurement of  $2^{\text{H}}\text{H}_2\text{O}$  excretion (saliva samples) it is possible to determine body tissue composition. It is estimated that approximately 1,400 women (700 IPTp-DP and 700 IPTp-DPAZ) will provide >90% to detect differences of 60g/week in gestational, weight gain, 0.4 kg m^2 in BMI, and 0.3 cm in post-partum MUAC.

**Laboratory assays:** We measure levels of maternal faecal calprotectin, a marker of enteric inflammation, in the third trimester, by freezing a small stool sample from the mother (-20 °C). Samples will be analysed within approximately 1 year of collection by suspending 0.1 g of thawed faeces in 5 mL extraction buffer and testing the supernatant using a standard enzyme-linked immunosorbent assay (ELISA) technique (CALPRO calprotectin ELISA Test, Calpro AS, Norway). We will also assess blood adipokines, specifically leptin and adiponectin (secretion correlates with fatty tissue mass) in the mother (from the blood sample collected at the scheduled third trimester visit) and newborn (cordblood). Maternal and cord EDTA plasma samples for leptin and adiponectin will be stored at -80°C prior to testing and measured by ELISA (R&D Systems USA). It is estimated that approximately 800 women (400 IPTp-DP, 400 IPTp-DPAZ) will provide >90% to detect differences of 100 µg/g and 2.28 ng/mL in calprotectin and leptin. Plasma aflatoxin-albumin adduct levels (AF-alb), will be measured using competitive binding ELISA, which is a sensitive and specific method for quantification of biologically effective aflatoxin in plasma reflecting exposure during the past 2-3 months.

#### 16.8.2 Malaria detection and molecular markers of antimalarial resistance

**COLLABORATING INSTITUTIONS AND CONTACT PERSONS:** Ass. [name] [name], University of Copenhagen

**OBJECTIVE:** 1. To evaluate the contribution of recrudescence and reinfection to prevalent and incidence of malaria infection over the course of pregnancy; 2. To investigate the prevalence of molecular antimalarial resistance markers in parasite isolates

**RATIONALE:** The use of DP, a slowly eliminated antimalarial, for IPTp may pose as a source of drug pressure that may drive the emergence of piperaquine resistance in sub-Saharan Africa. To evaluate this, we will conduct molecular studies to detect malaria infections from enrolment to delivery, differentiate these as new or recrudescence infections and determine their molecular resistance status to artemisinins and piperaquine.

#### **METHODS**

**Diagnostic qPCR:** Dry blood spots or redcell pellets will be prepared at enrolment, all unscheduled (sick) visits and at delivery from all women and from a random sub-sample of approximately 1,464 asymptomatic women at each scheduled monthly follow-up visit. DNA will be extracted using chelex-100 extraction or Qiagen DNA extraction for further qPCR targeting the high-copy telomere-associated repetitive element 2 (limit of detection 0.15 parasites/µl blood).

**Genotyping distinguish recrudescence and re-infections:** qPCR positive samples from women at two sequential monthly visits will be used for PCR genotyping of the polymorphic *P. falciparum* genes MSP2, GLURP and MSP1; interpretation of results will be performed using standardised methodologies.

**Molecular markers of antimalarial drug resistance:** All *P. falciparum*-qPCR positive samples collected will be used for the evaluation of artemisinin, piperaquine, and SP resistance molecular markers. All PCR positive samples at enrolment will be examined for SNPs in the genes *Pfdhfr*, *Pfdhps* (*SP arm*), *K13* and *Pfmdr-1* and plasmepsin 2,3 (DP arms). A high-throughput next-generation platform for targeted sequencing using Illumina®-based technology will be applied as the main method. After index PCR, the gene fragments will be sequenced using the Illumina Miseq® platform available through collaboration with researchers at the Danish Technical University, Denmark. In addition, direct Sanger sequencing methods will be applied to a subset of samples (approximately 200) targeting mainly *K13* to confirm novel findings and as a gold standard comparison using published PCR methods [6] and after PCR, also send for commercial sequencing. A PCR sequence-specific oligonucleotide probe (SSOP)-ELISA will be deployed as a reference method to the Illumina methodology regarding *Pfdhfr* and *Pfdhps* data.

**Data analysis:** The degree of SP resistance in the parasite population will be expressed as the frequency of the *Pfdhps*-A437G, K540E, or A581G mutations, which predict the frequency of quadruple, quintuple, and sextuple *Pfdhfr*-*Pfdhps* mutant haplotypes, respectively. In addition, we will assess prevalence of molecular markers associated with tolerance/resistance to artemisinin and piperaquine (*K13* and *Pfmdr1*, plasmepsin-2). These molecular data will be used as potential effect modifiers in the impact analysis of the main trial.

**Microbiome:** We will assess the impact on the intestinal and vaginal microbiome using Illumina MiSeq sequencing with V3 cassettes – including coverage of V1, V2, V5 and V6 regions of the 16S rDNA gene – with stool and vaginal-swab samples collected among women from selected sites at enrolment and, again, in the third trimester; stool samples from the newborns of these same women will be collected at 6 to 8 weeks post-partum. A random selection of 20 samples will have 87% power to detect a 10% difference in alpha-diversity (5 vs 4.5) (SD 0.5,  $\alpha=0.05$ ). Thus, 300 total samples collected across all three treatment groups at each of the five time points will be randomly selected and run with mixed mock community controls to permit improved genus quantification across MiSeq runs, and for diversity and precision-sensitivity analyses. Additional panels of Real-Time PCRs will be run. Sequences from microbiota samples will be binned in operational taxonomic units sharing  $\geq 97\%$  nucleotide sequence identity, and assigned a taxonomy based on the naïve Bayesian RDP classifier. Analyses will then determine whether exposure to study drug during pregnancy alters the composition of the microbiota or the relationship between maternal and infant microbiota structure. Degrees of similarity between pairs of maternal-infant faecal microbiota samples will be computed using the phylogeny-based UniFrac metric. In addition to whole community similarity between mother and infant, computational methods will be applied to identify bacterial species shared between mothers and infants, and the degree to which this varies by treatment group. Microbiota analyses will consist of a semi-quantitative indication of the relative amounts of bacterial species. Pooled DNA will be used to screen for antimicrobial resistance with a multiplexed real-time PCR to detect *msr(A)*, *mef(A)*, 23S rRNA variation by identifying *erm* genes and mutations in the *mtrR* promoter regions and *ere(A)* and *ere(B)* genes. Markers of gut inflammation will be measured in maternal stool and sera (e.g. calprotectin).

**Macrolide resistance:** This component will assess the effects of repeated AZ dosing on macrolide resistance. Naso-pharyngeal samples will be collected at enrolment, near delivery (collected at the last scheduled visit around 36-40 weeks gestational age or at delivery, or 6 to 8 weeks post-delivery and at 6 month or later. The prevalence of pneumococcal carriage in the general population in western Kenya is 27-43%. Using a conservative estimate that 25% of women are colonized, and allowing for 13.7% lost to follow-up, 344 women per arm, or 1,032 women in total will have 80%

power to detect a 10%- point difference in the incidence of resistance between baseline and follow-up, assuming that 5% of women have macrolide resistant *Pneumococcus* at baseline, and no increase is seen in the non-azithromycin arms. If only 10% or 15% of women are colonized with pneumococcus, this sample size will be sufficient to detect a 22.3% and 16.0% difference. Nasopharyngeal samples will be collected on FLOQSwabs™ (Copan) and stored at -80°C in STGG media until processing. Culture methods will be used to identify *Pneumococcus*; e-test or broth microdilution will be used to assess changes in resistance patterns associated with SP and AZ.

#### 16.8.4 *Maternal antibody, trans-placental antibody transfer and multi-pathogen neonatal cell mediated immune responses*

**COLLABORATING INSTITUTIONS AND CONTACT PERSONS:** Ass [name], University of Massachusetts, Worcester, USA and [name], University of Melbourne, Australia.

**OBJECTIVE:** To determine if antimalarial treatment of women during pregnancy is associated with changed maternal immunity, robust transfer of maternal antibodies and the development of cell-mediated immunity in infants to other pathogens, in addition to malaria.

**RATIONALE:** Maternal antibodies may protect pregnant women from malaria, but placental malaria has been associated with impaired transfer of maternal antibodies and hypergammaglobulinemia. This negatively impacts the new-born's ability to be protected against malaria as well as viral infections. The scope of this lack of maternal antibody protection tends to be studied one or two infections at a time. Using multiplex methods, we will be able to simultaneously measure a panel of antibody titres and cell-mediated immune responses to multiple pathogens within the same study participants using extremely low volumes of peripheral blood.

#### **METHODS**

a) *Serology profiling:* Using a Luminex, multiplex suspension bead-based assay to simultaneously measure antibody titers to a panel of individual antigens or immunologic peptides against malaria (ie MSP1, AMA1, CSP, LSA1, etc), EBV, CMV, measles virus, tetanus toxoid, arboviruses etc. We will use a Systems Serology approach to identify protective antibodies.

b) *Cell-mediated immunity:* Using multi-parameter flow cytometry and potentially single cell RNAseq we will efficiently and comprehensively interrogate immunity specific to pathogens and EPI vaccine-induced responses.

*Sample size:* ~1,500, all scheduled clinic visits, delivery and 1, and 6-8 weeks infant visit (heel prick)

#### 16.8.5 *IPTp and maternal immune modulation*

**COLLABORATING INSTITUTIONS AND CONTACT PERSONS:** [name], University of Melbourne

**OBJECTIVE:** To examine effects of IPTp with DP, DPAZ and SP on maternal immune activation and pathogen clearance.

**RATIONALE:** The beneficial effect of AZ extends beyond malaria control. To explain our surprising and important results, we will test new hypotheses regarding effects of AZ and SP on immunomodulation. We postulate that AZ will decrease cytokine elicitation, especially of macrophage derived inflammatory cytokines, from PBMCs.

**METHODS:** a) *Clinical sampling.* 100 study participants, one third from each arm, matched for gravidity. Peripheral blood (as part of the standard study sample described in the main text) will be

collected at enrolment, at second treatment visit and at the last scheduled visit (around) 36 weeks' gestation for PBMCs, whole blood and plasma CRP. Stool, PBMC, plasma and RBC will be frozen.

*b) Modulating maternal innate immune responses to malaria and other infections.* PBMC cytokine responses to infected erythrocytes (IE) and to LPS will be compared between the three arms. IE (CS2 line, associated with placental malaria) will be added at a 3:1 ratio to PBMCs, and LPS at 100 ng/ml. PHA is used as viability control.

*c) Altered phagocytic clearance.* To determine whether AZ and/or SP augments the clearance of IE and bacteria, we will use our whole blood assay. Fresh whole blood will be analysed by flow cytometer and  $1.5 \times 10^5$  phagocytes will be suspended in 100  $\mu$ L with ethidium bromide labeled IE (25:1) for 30 mins, or with  $2 \times 10^8$  *E. coli* pHRODO for 10 mins at 37°C, or 4°C (control). After counterstaining with FITC-CD14 and CD16-APC, proportion of monocytes taking up IE or *E. coli* is determined. Monocyte subsets (classical, intermediate and non-classical) will be determined. We hypothesise that azithromycin, through its effect on phagocytic function, alters the uptake of parasites and/or bacteria, potentially affecting clearance of these infections.

*Data analysis and sample sizes:* Paired samples will be collected at enrolment, the next monthly and the last monthly scheduled visit during pregnancy. We will perform paired (within subject) and between-subject (SP, DHA-PQ or DHA-PQ + AZ) unmatched comparisons. Based on previous observations the study has approximately 80% power to detect a 50% reduction in cytokine output between groups.

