### **9.3 STATISTICAL METHODS**

#### **9.3.1 General principles**

All statistical analyses will be described in detail in the Statistical Analysis Plan (SAP) and finalised and signed before unblinding the study. One interim analysis and/or one sample size re-estimation will be conducted as described in sections 7.6.1.2, page 37 and 10.1.3, page 45. The study is designed as a superiority trial, so all tests will be two-sided and  $P$ -values  $<0.05$  will be used to define statistical significance. Analysis will be done using SAS and Stata.

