### 9.3.2.2 Secondary endpoints analyses

These will also be analysed using GLMs with the treatment arm as the single predictor and country (Kenya, Malawi and Tanzania) and gravidity (pauci and multigravidae) as control variables. The point estimate of the treatment effects with 95% CI will be derived via specification of a GLM model for each secondary outcome depending on its distribution. For a binary outcome such as the components of primary endpoint, similar analysis to the primary endpoint analysis will be performed and the treatment effects measured as RR will be generated. For a continuous outcome like birthweight, a Gaussian distribution will be assumed and identity link function will be used. Correspondingly the mean difference and its 95%CI between two arms will be calculated. For a count outcome such as the number of SAEs, Poisson distribution and log link function will be used, from which incidence rate ratio (IRR) and its 95% CI will be computed.

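### Immune-modulation sub-study (16.8.5): the between-arm comparison, as worded, adjusts for neither the enrolment sample nor gravidity, so it is valid but less efficient than it could be, and the within-woman tests have no control arm

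*Protocol*

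**What the plan says.** All of the following is in the protocol.

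- **Aim (16.8.5, Objective):** "To examine effects of IPTp with DP, DPAZ and SP on maternal immune activation and pathogen clearance".
- **Who is sampled (16.8.5, Methods a):** "100 study participants, one third from each arm, matched for gravidity".
- **When (16.8.5, Data analysis and sample sizes):** "Paired samples will be collected at enrolment, the next monthly and the last monthly scheduled visit during pregnancy". Methods (a) puts the last sample at around 36 weeks' gestation.
- **Arm comparison (16.8.5, Methods b):** "PBMC cytokine responses to infected erythrocytes (IE) and to LPS will be compared between the three arms".
- **Analysis (16.8.5, Data analysis and sample sizes):** "We will perform paired (within subject) and between-subject (SP, DHA-PQ or DHA-PQ + AZ) unmatched comparisons".
- **Power (same paragraph):** "the study has approximately 80% power to detect a 50% reduction in cytokine output between groups". The basis is given only as previous observations. No standard deviation, alpha or correlation is stated.
- **Trial-wide rules:** section 9.3.1 says "The study is designed as a superiority trial, so all tests will be two-sided", with significance at 0.05. On secondary endpoints, section 9.3.2.2 says "These will also be analysed using GLMs with the treatment arm as the single predictor and country", and the sentence goes on to name gravidity as the second control variable. It does not mention a baseline value of the outcome.

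**The concern.** The sub-study has two assets for comparing the arms: a sample from each woman at enrolment, and arms balanced on gravidity. Section 8.1 treats gravidity as the main known modifier of susceptibility to malaria. The sentence that fixes the analysis uses neither asset in the comparison between arms. The only stated use of the enrolment sample is a within-woman comparison over time.

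Two things follow. First, precision that costs nothing is left unused in a sub-study whose stated power has no margin above about 80%. Second, the within-woman test has no concurrent control. Enrolment is at 16 to 28 weeks (7.2.1) and the last sample at about 36 weeks, so 8 to 20 weeks of pregnancy separate the two. A change that pregnancy produces in every arm would appear in that test alongside any drug effect. If some arms then showed a significant change and others did not, a reader could take the pattern for a difference between drugs.

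**Working it through.** **Inputs.** From the protocol: 100 women in three arms, so about n = 33 per arm; a 50% reduction, which is a log ratio of ln 2 = 0.693; power of about 80%; two-sided alpha 0.05 (9.3.1, because 16.8.5 states none). Not in the protocol, and therefore assumed: the within-woman correlation r between enrolment and follow-up (range 0.2 to 0.7), the share of variance R² explained by gravidity (0.02 to 0.10), and the size of any gestational shift.

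**Step 1: the stated 80%.** It cannot be reproduced independently because no SD is given; it can only be back-solved. For an unadjusted two-sample comparison:

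- standardised difference = (1.960 + 0.842) × √(2/33) = 2.802 × 0.2462 = 0.690
- implied SD on the log scale = 0.693 / 0.690 = 1.005

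The t distribution gives nearly the same result (0.70 and 0.99).

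**Step 2: adjust for the enrolment value.** Adjustment multiplies the residual SD by √(1 − r²), so power = Φ(2.802/√(1 − r²) − 1.960).

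| r | 0.2 | 0.3 | 0.4 | 0.5 | 0.6 | 0.7 |
|---|---|---|---|---|---|---|
| Power, adjusted for enrolment value | 81.6% | 83.6% | 86.4% | 89.9% | 93.8% | 97.5% |
| Gain over 80% (points) | 1.6 | 3.6 | 6.4 | 9.9 | 13.8 | 17.5 |

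A t-based version with one degree of freedom fewer agrees to within 0.1 point.

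**Step 3: adjust for gravidity alone.** Power = Φ(2.802/√(1 − R²) − 1.960). This gives 80.8%, 82.0% and 84.0% for R² = 0.02, 0.05 and 0.10, a gain of about 1 to 4 points. A 10-point gain from gravidity alone would need R² = 0.25 (89.9%).

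**Step 4: if the unmatched comparison were made on changes from enrolment.** The SD is then multiplied by √(2(1 − r)). Power is 60.1%, 65.8%, 80.0% and 95.1% at r = 0.2, 0.3, 0.5 and 0.7. Each figure is below the adjusted power at the same r.

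**Step 5: the within-woman test when the drug does nothing.** With 33 women and r = 0.5, the standard error of the mean change, in SD units, is √(2 × 0.5/33) = 0.174. If pregnancy alone shifts the mean by δ SD, the rejection rate is Φ(δ/0.174 − 1.960) + Φ(−δ/0.174 − 1.960).

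| Assumed shift δ | 0.1 SD | 0.2 SD | 0.3 SD |
|---|---|---|---|
| P(significant change) | 9% | 21% | 41% |

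The nominal rate is 5%. These figures illustrate the mechanism; the protocol gives no estimate of the shift.

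**The case against.** **Matched may mean balanced.** No matched sets are described, and 100 does not divide into triplets. The natural reading is group balance on gravidity, and for that an unmatched test on independent women is not an error. This stands. The criticism is one of efficiency, and little of it concerns gravidity.

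**Gravidity may already be covered.** Section 9.3.2.2 controls secondary endpoints for country and gravidity. If that model governs here, the gravidity part falls away. But 16.8.5 states its own analysis, and the two texts do not agree. Neither adjusts for the enrolment value, where nearly all of the gain lies.

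**The comparison might use changes from enrolment.** The text does not say which values are compared, so one cannot claim that the enrolment sample is certainly ignored. By step 4, change scores would still be less efficient than adjustment and would fall below 80% when r is under 0.5.

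**This is detail for the analysis plan.** Section 9.3.1 defers detail to that plan, which is not at hand. That would answer a silence. Here the appendix names the comparisons, and a better choice is available from the same data.

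**The protocol does not treat within-woman change as a drug effect.** A reader might infer that it does. The text does not support this: 16.8.5 gives no rule for interpreting the paired tests, Methods (b) plans a comparison between arms, and the power statement is between groups. What stands is narrower: a before/after test without a control cannot carry treatment inference, and the text does not say that it will not be asked to.

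**Conclusion.** The point holds as one of efficiency and labelling. The between-arm comparison in 16.8.5 is valid. As worded, it leaves unused the enrolment value and the gravidity on which the arms are balanced. Using the enrolment value would raise power from the stated 80% to about 82% to 98% for r from 0.2 to 0.7, a gain of about 2 to 18 points; gravidity alone is worth about 1 to 4 points. Both ranges rest on assumed r and R², and on taking the stated 80% as the power of an unadjusted comparison.

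Two stronger readings are not supported. A single loss of about 10 points requires r = 0.5, which the protocol does not give. Attributing the loss to ignored matching is also wrong, because most of it comes from the unused enrolment value.

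The within-subject tests cannot separate drug effect from gestational change. That limits what they can show, but it is not evidence that the protocol misreads them.

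The sub-study involves about 100 of 4,680 women (2.1%) and is not among the key secondary outcomes in 7.4.2. The primary result is not affected.

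**What to change.** In 16.8.5, replace the sentence on comparisons with wording to this effect:

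> The main analysis compares the arms by linear regression of log cytokine output, and separately of phagocytic uptake, at each follow-up visit on treatment arm, adjusted for the enrolment value of the same measure and for gravidity group. Within-subject changes are descriptive and are not interpreted as treatment effects.

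This also brings the appendix into line with the gravidity control in 9.3.2.2. Restate the power on this basis, giving the SD, alpha and correlation that it assumes.

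The cost is a wording change in Appendix VII. The enrolment samples and gravidity are already collected. The one new requirement is a stated rule for women with no usable enrolment assay, since a regression that simply drops them would lose part of a small sample.
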